# What is the effectiveness and safety of mirtazapine versus escitalopram in alleviating cancer-associated poly-symptomatology (the MIR-P study)? A mixed-method randomized controlled trial protocol

**DOI:** 10.1186/s12904-022-00976-7

**Published:** 2022-05-23

**Keywords:** Signs and Symptoms, Neoplasms, Advanced cancer, Palliative Care, Antidepressive Agents, Polysymptomatology, Cancer pain

## Abstract

**Background:**

Advanced cancer patients often experience multiple symptoms at a same time. This might lead to polypharmacy and increase adverse events representing major threats to the quality of health care, especially in palliative care situations. Mirtazapine, an antidepressant agent, has been suggested as a potential relevant drug to alleviate multiple cancer-related symptoms at a same time.

Therefore, the present study aims to assess the effectiveness of mirtazapine in alleviating multiple symptoms at a same time in advanced cancer patients suffering from a major depressive episode compared to a group receiving escitalopram, another antidepressant agent.

**Methods:**

Multicentre, prospective, randomized, controlled trial in 12 palliative care services in France.

The study will be based on a mixed-method methodology using parallel groups, of oral mirtazapine compared with oral escitalopram, with a 56 day follow-up. The primary outcome will be an improvement of the Global health Status (issued from the EORTC-QLQ-C30) on day 56. 418 participants will be clinically followed-up on day 7 and 56 and will have a telephonic assessment on days 14 and 28. A sub-sample of participants will be invited to take part in semi-structured qualitative interviews at baseline and day 56. For the qualitative part, purposeful sampling will be used.

**Discussion:**

This study will provide evidence for the pharmaceutics management of poly-symptomatology in advanced cancer patients. This could lead to important changes in the management of those patients by using a single molecule to alleviate multiple symptoms at a same time, potentially improving medication adherence, symptoms’ control, and reducing the risk of medications adverse events.

**Trial registration:**

Trial registration: NCT04763135. Registered 18 March 2021.

## Background

Despite continuous progress in cancer specific treatments, cancer remains the first leading cause of death in European countries. Therefore, the scientific community has an increasing interest in improving cancer patient’s quality of life [1, 2].

Cancer patients are highly burdened by symptoms with variability depending on cancer site, stage, disease trajectory, and cancer treatments [3, 4]. This burden worsens with the disease progression. For this reason, advanced cancer patients very often experience symptoms altering their quality of life, while the aim, at this stage, is to improve it. Indeed, more than half of advanced cancer patients experience fatigue, pain, lack of energy, tiredness or lack of appetite. Unfortunately, as patients often experience multiple symptoms at the same time, they might need multiple drugs, resulting in higher risk of adverse event or drug interactions [5, 6]. A potential solution to avoid such an issue might be to use a single drug to target multiple symptoms at the same time. Additionally, very few treatments are available for some symptoms, for instance, no treatment is currently licensed in Europe for breathlessness and a very few are available for lack of appetite or loss of weight.

Mirtazapine is a licensed anti-depressive treatment, advocated to be an eligible drug in treating multiple cancer related symptoms [7, 8]. Indeed, mirtazapine has an α-2 adrenergic activity which increases noradrenergic and serotoninergic central neurotransmitters, leading to its short-term effect on acute depressive disorders [9]. Besides this α-2 adrenergic activity, mirtazapine also links to 5HT3 receptors and H1 receptors. This activity on various central and periphery receptors might have various effects on appetite, sleep disorders, pruritus, emesis, breathlessness and other multiple symptoms. Numerous recent studies gave additional clinical argument to support mirtazapine as an effective treatment for sleep disorders [10], breathlessness [11], and lack of appetite in advanced cancer patients [12].

Unfortunately, our previously published review highlighted that, despite encouraging results in various symptoms, evidence for the effectiveness of mirtazapine in improving quality of life in cancer patients experiencing poly-symptomatology is still lacking of robust randomized controlled trials [13].

Because health-related quality of life is a highly associated with the level of burden driven by symptoms; our research aims to assess the effectiveness of mirtazapine in improving health-related quality-of-life (HRQoL) in advanced cancer patients experiencing poly-symptomatology.

### Hypothesis

We hypothesize that oral mirtazapine is superior to another antidepressant drug (oral escitalopram) in improving health-related quality of life of poly-symptomatic advanced cancer patients suffering from depression.

### Objectives

The primary objective will be to assess the effectiveness of oral mirtazapine in improving HRQoL in poly-symptomatic advanced cancer patients suffering from depression after 56 days of treatment, compared with oral escitalopram.

The secondary objectives are:

i- To assess the effectiveness of oral mirtazapine in poly-symptomatic advanced cancer patients suffering from depression compared with escitalopram on the following outcomes:The experience of poly-symptomatology, poly-medication, and taking antidepressant agents and explore the dynamic of this experience between inclusion and 56 days.The improvement of the following symptom intensity: depressive mood, pain, nausea, lack of appetite, vomiting, breathlessness, sleep disorders and anxiety at 28 and 56 days.The improvement of the different functional capacities at 56 days.The mitigation of the loss of weight at 28 and 56 days.The use of medications to treat associated symptoms at 28 and 56 days.

ii- To assess the safety of oral mirtazapine in poly-symptomatic advanced cancer patients suffering from depression compared with escitalopram from 7 days.

iii- To assess the compliance to the treatments.

## Methods

The trial will be a multicenter, prospective, randomized, open-labelled, controlled trial based on a mixed-method methodology using parallel groups, of oral mirtazapine (intervention) compared with oral escitalopram (control), with a 56-day follow-up. Semi-structures interviews will be performed on a purposive sample for qualitative outcomes. The 418 participants will be followed-up on day 7, 14, 28 and 56 for a 56-day period. A sub-group of participants will be invited to take part in qualitative interviews at baseline and day 56. Recruitment of participants for the qualitative part will be based on a purposive sampling. An overview of the study (Fig. 1) and an overview of the study events (Table 1) are provided below.

**Fig. 1 Fig1:**
[figure not shown]
Overview of the study

**Table 1 Tab1:** Overview of the study events for each participant during the follow-up period

***STEPS***	***Screening***	***Inclusion*** ***Randomisation***	***V2*** ***Telephone call***	***V3*** ***Telephone call***	***V4*** ***Clinical assessment***^c^	***V5*** ***Clinical assessment***^c^
***Time***	***J-14 à J-2***	***J0***	***J7*** ** ± *****1 j***	***J14*** ** ± *****1 j***	***J28***** ± *****3 j***	***J56***** ± *****3 j***
***Actions***						
***Inclusion and non-inclusion criteria***	*X*	*X*				
***ECG et postural hypotension test***		*X*				
***Study information delivery***	*X*	*X*				
***Informed consent***		*X*				
***MADRS***	*X*	*(X)*^b^			*X*	*X*
***HADS-D***	*X*	*(X)*^b^			*X*	*X*
***QLQ-C30***		*X*			*X*	*X*
***ESAS12-F***		*X*			*X*	*X*
***ASEC***		*X*	*X*	*X*	*X*	*X*
***Factor 1 of the MARS***					*X*	*X*
***Clinical assessment: weight, blood pressure, Performans Status***		*X*			*X*	*X*
***Treatment list***		*X*			*X*	*X*
***Sociodemographic data***^a^		*X*				
***Randomisation***		*X*				
***Treatment doses adaptation***		*X*	*(X)*	*X*	*X*	*X*
***Adhesion to treatment assessment (pill count)***					*X*	*X*
***Semi-structured interviews***		*X*				*X*
***Side effects***		*X*	*X*	*X*	*X*	*X*

^a^***Socio-demographics:**** date of birth, marital status, number of children, declared level of autonomy/dependence, professional position, way of life, kind of home support, cancer type, stage of the cancer, prior and current cancer treatments, personal background of psychotropic drugs use, the existence of a psychological or nutritional follow-up (and frequency of it)*

^b^***HADS-D/MADRS:**** if not available at the time of screening or older than 7 days old*

^c^***Clinical assessment:**** might be performed using teleconsultation if needed*

### Population

Our study has interest in the population of adult patients suffering from an advanced cancer, who are diagnosed from a depressive syndrome and are experiencing at least another symptom.

### Sample Size

Based on an expected standard deviation of 26 in our primary outcome (The Global health Status), and considering a correlation of 0.5 between inclusion and day 56 (corresponding in a standard deviation of the variation of the GHS score of 26 between baseline and day 56), and expecting a moderately clinically significant difference of 8 points between groups, it will be necessary to include 418 participants (bilateral test, alpha risk of 0.05, power of 0.8, attrition 0.2).

Considering the risk of lost to follow-up due to our population global condition, we considered an attrition rate of 20% when calculate the sample size.

### Inclusion and non-inclusion criteria

Inclusion and non-inclusion criteria are summarized in Table 2.

**Table 2 Tab2:** Inclusion and non-inclusion criteria

Inclusion criteria	Non-inclusion criteria
Being over 18 years old	Being treated with an antidepressant agent during the four weeks before inclusion
Suffering from an advanced cancer	Having had a hypersensivity event to mirtazapine, escitalopram of any excipient
Having a clinically estimated life expectancy over 3 months	Having had a prior inefficient treatment with mirtazapine or escitalopram
	Having postural hypotension or arterial systolic hypotension inferior to 90 mmHg measured following the guidelines of the European Society of Cardiology
Being diagnosed from having a depressive syndrome by a Hospital Anxiety and Depression Scale-D over 11	Having a QT interval over 420 ms
	Having uncontrolled heart rhythm disorder or uncontrolled conduction disorder
Being in need of an antidepressant treatment	Having had or having bipolar disorder
Suffering from at least one under-controlled symptom (defined as a score over 3 on the Edmonton Symptom Assessment Scale) among: pain, nausea, vomiting, breathlessness, lack of appetite, sleep disorders, or anxiety	Having uncontrolled seizure or epilepsy (relative non-inclusion criteria needing a neurology specialist opinion)
	Having or having a history of closed-angle glaucoma
Having or not a cancer treatment	Having bone marrow aplasia
Being able to understand the information related to the study, and to sign informed consent	Practicing breastfeeding or being pregnant
Having agreed to take part in the study	Women of childbearing age with no contraception method
	Having a treatment with: - Monoamine oxidase inhibitors (Selegiline, Moclobemide, Isocarboxazid, Nialamide, Phenelzine, Tranylcypromine, Iproniazid, Iproclozide, Toloxatone, Linezolid, Safinamide, Rasagiline) - One of the following antiarrhythmic drugs: Flecainde, Propafenone, any class IA and III antiarrhythmic drug (amiodarone, disopyramide, hydroquinidine, quinidine, procainamide, sparteine, ajmaline, prajmaline, lorajmine, bretylium tosilate, bunaftine, dofetilide, ibutilide, tedisamil, dronedarone) - Antipsychotic drugs (phenothyazine antipsychotics, pimozide, haloperidol) - Linezolid, sparfloxacin, moxifloxacin, macrolids (IV erythromycin, josamycin, clarithromycin, telithromycin), pentamidin, halofantrine, HIV protease inhibitors (ritonavir, nelfinavir, amprenavir, indinavir), azolic antifungal agents (ketoconazole, itraconazole, miconazole, fluconazole, voriconazole) - Mizolastine and Cimetidine - Ticlopidine - Metoprolol - Methadone - Ketamine - Triptan drugs - Dapoxetine - St. John's wort - Antidepressant drug - Any other medication known to cause prolonged QT intervals
Being able to fill Patient Reported Outcomes questionnaires	Having genetic galactose intolerance or glucose-galactose malabsorption
	Having one of the following electrolyte disorders not corrected at the time of inclusion: hyponatremia, hyperkalemia, hypokalemia, hypermagnesemia, and hypomagnesemia
Being available to be called on days 7 and 14	Having end-stage renal disease with a creatinine clearance inferior to 15 ml/min calculated using the Cockroft’s formula
	Having hepatic failure
Having a social security affiliation	Having legal incapacity

There is no unanimous definition of advanced cancer. Scientific societies mainly agree to define advanced cancer as conditions that cannot be cured in the current state or science (Canadian cancer society, ESMO, [14]. However, they disagree with including the metastatic status (ESMO, [14]), impossibility to perform surgery (ESMO), or lack of response to first line treatments (CCS).

Based on these various definitions, in our study, we will rely on the following definition: “cancers that cannot be cured, and that, in the case of metastatic cancer, have usually spread from where they started to other parts of the body.”, [15] in addition to “cancers that progress after a second line specific treatment or primary location of cancer that is unresectable”.

Patients will be considered to have a depressive syndrome if their Hospital Anxiety and Depression Scale-D score rates over 11(37), and if the clinical assessment supported by the results from the Montgomery and Åsberg Depression Ratting Scale (38), confirm the diagnosis and the need for an antidepressant treatment.

### Recruitment sites

Eleven French centers will handle recruitment. All centers have specialized palliative care services on site, including a palliative care unit. All of them take care of advanced cancer patients on a regular basis. The centers are seven University Hospitals, two Comprehensive Cancer Centers, one Public Hospital and one non-profit private hospital.

For practical justifications, the recruitment for the qualitative part of the study will be made only in one center. Centers are located in various French regions.

### Study procedure

#### Recruitment and inclusion procedure

A screening for potential participants will be made by clinical teams in oncology or palliative care, during consultations, day hospital or conventional hospitalization. The principal investigator will be informed of every potential participant. He will verify inclusion and non-inclusion criteria. If the potential participant fulfils all requirements, the principal investigator will meet the patient to give information about the study (and about the qualitative part of it if needed).

Then the participant will be called at least 48 h after having received the oral and written information. They will be asked if they want to part to the study. If positive, an appointment for inclusion, randomization and baseline assessment will be booked. At inclusion, participants will sign an informed consent to participate. For those who will take part in the qualitative part, they will receive separate information and sign a specific consent form.

At inclusion, participants will be clinically examined with a postural hypotension test and an ECG if no prior ECG is available. If the participant does not have any non-inclusion criteria, he will be enrolled in the study and receive an anonymity code generated by the ENNOV Clinical software. Socio-demographic data will be collected. The participant will have to fulfil the EORTC QLQ-C30, Hospital Anxiety and Depression Scale –Depression (HADS-D), Edmonton Symptom Assessment Scale 12 French (ESAS-12F), and Antidepressive Side-Effect Checklist (ASEC) questionnaires. The principal investigator will fulfil the MADRS questionnaire and assess the patient’s Performance Status. If needed, the principal investigator will be able to ask for a psychiatric opinion.

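### The inclusion ECG is waived whenever an earlier one exists, with no age limit, so an outdated tracing could clear the QT exclusion; Table 1 shows the ECG at J0 without condition

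*Protocol article*

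**What the plan says.** - **Recruitment and inclusion procedure.** Before the information meeting, the investigator checks eligibility: "He will verify inclusion and non-inclusion criteria". At the inclusion visit the patient has a postural hypotension test and "an ECG if no prior ECG is available". Enrolment then follows if no non-inclusion criterion is present.
- **Table 2.** The non-inclusion criteria include "Having a QT interval over 420 ms", with no statement of when the QT must have been measured. Related criteria are "Having uncontrolled heart rhythm disorder or uncontrolled conduction disorder", "Any other medication known to cause prolonged QT intervals", and, for electrolytes, "Having one of the following electrolyte disorders not corrected at the time of inclusion".
- **Table 1.** The row "Inclusion and non-inclusion criteria" is marked at screening (J-14 to J-2) and at J0. The row "ECG et postural hypotension test" is marked at J0 only, with a plain X and no footnote. HADS-D and MADRS are shown at J0 as a bracketed (X). Their note b requires them to be repeated if they were not available at screening or are more than 7 days old.

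**The concern.** The QT limit is a safety exclusion, and both the drug list and the electrolyte criterion in Table 2 show that the sponsor treats QT prolongation as a hazard. A safety exclusion works only if the measurement behind it is current. The procedure text lets any available tracing replace the inclusion ECG and does not date that tracing. Patients have advanced cancer, with or without cancer treatment, so drugs and electrolytes may well have changed since an old ECG. A patient whose QT has since risen above 420 ms could be enrolled with the exclusion undetected. A site that follows the text and a site that follows Table 1 could also act differently.

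**Working it through.** There is no figure in the plan to reproduce. The check sets the places side by side.

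**1. What decides whether an ECG is done at J0?**

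| Place | Condition for the J0 assessment | Age limit on an earlier result |
|---|---|---|
| Procedure text, ECG | Only if none is available | None stated |
| Table 1, ECG row | Plain X, no condition | Not applicable |
| Table 1, HADS-D/MADRS | (X), note b | 7 days |
| Table 2, QT criterion | Not stated | None stated |
| Table 2, electrolytes | Status at inclusion | Current by definition |

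For HADS-D/MADRS the authors gave both halves of a substitution rule: availability and age. For the ECG the text gives availability only.

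**2. How old can the tracing be at J0?**

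- As written: no upper bound.
- If the prior ECG means one recorded in the screening period (J-14 to J-2): between 0 − (−2) = 2 days and 0 − (−14) = 14 days.
- Under a window of J-14 to J0: at most 14 days.

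**3. Does the schedule supply a dated ECG elsewhere?** In Table 1, eligibility is marked at 2 time points (screening and J0) and the ECG at 1 (J0). No ECG is marked at screening, so Table 1 does not establish that the prior ECG is a screening ECG. No ECG is marked at any of the 4 follow-up contacts (J7, J14, J28, J56), so a QT missed at inclusion has no later scheduled check.

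**4. Do the other exclusions replace the measurement?** Excluding QT-prolonging drugs, uncorrected electrolyte disorders and uncontrolled rhythm or conduction disorders removes several causes of a long QT. It does not establish that the QT is at or below 420 ms on the day of inclusion.

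**5. How many patients?** This would need the share of patients with a prior ECG, the age of those tracings, and the share who would now exceed 420 ms. The article gives none of the three, so no estimate is possible.

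**The case against.** The strongest reply is that this is one clause in a condensed article. The acceptable age of a prior ECG may well be set in the full protocol, which is not shown. That is possible, and it limits confidence. However, the article does more than stay silent: it prints a working rule for skipping the ECG, and that rule is too wide as printed.

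The second reply is that Table 1 marks the ECG at J0 with a plain X, and by the table's own convention a conditional item would be bracketed. If the table governs, every patient has an ECG at J0 and the gap closes. This stands in part, and it is one reason to offer the table's version as a fix. It does not settle the matter, because the same row also holds the postural test, which is unconditional, and because the text states the waiver explicitly. For the same reason a reader should not infer a proven contradiction between text and table: the X may belong to the postural test alone.

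The third reply is that the prior ECG is naturally the one seen when the criteria are checked at screening, and so at most about two weeks old. That is a reasonable guess at the intention. No sentence says so, and a criteria check in that period can itself rest on an older tracing.

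Finally, the criterion still binds at inclusion. That is correct, but the waiver determines the evidence on which it is judged.

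**Conclusion.** The point holds as a defect in a stated eligibility rule. Taken literally, the procedure text allows an undated earlier ECG to clear the QT exclusion, and it does not sit well with the plain J0 mark in Table 1. It should be corrected, with medium confidence, because the full protocol may already contain a window.

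A reader might infer that patients with a QT over 420 ms will in fact be enrolled, or that the sponsor meant to accept tracings of any age. The documents support neither. They give no count, the other exclusions reduce the risk, and a benign reading of the clause is available. The point concerns patient safety at entry. It does not affect the primary outcome, the randomization, the sample size or the analysis.

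**What to change.** Choose one of two rules and state it in the recruitment and inclusion procedure:

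1. Record an ECG at J0 for every patient, as Table 1 shows, and delete the waiver.
2. Accept a prior ECG only if it was recorded within a stated window and there has been no change in QT-relevant drugs or electrolytes since; otherwise record one at J0. The J-14 to J0 period is a suggestion that fits the existing screening window. The exact limit is an assumption for the sponsor to confirm.

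In Table 1, put the ECG on its own row, separate from the postural test. Under rule 2, mark it (X) with a footnote giving the window, in the manner of note b.

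The cost is an ECG at the existing J0 visit for patients without a recent tracing (for all patients under rule 1), one amended sentence, and one split table row with, under rule 2, a footnote. If the full protocol already sets a window, only the wording needs to change.

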#### Randomization

On the day on inclusion, participants will be randomly assigned to one of the two arms of the study by the ENNOV Clinical software. We will use the minimization method. Due to the important influence on quality of life, the Performance status, and the number of symptoms for which intensity is over 3 will be considered during randomization. The inclusion centre will also be considered.

#### Intervention and comparator

Mirtazapine will be compared to another antidepressant drug to avoid confusion bias in improving health-related quality of life due to the lone antidepressant effect of mirtazapine. Escitalopram has been chosen as a comparator because it is, like mirtazapine, effective in treating depression in advanced cancer [16], with few medication interactions [17], but no effect on poly-symptomatology is expected.

Both drugs will be used following the usual practice for depression. They will be introduced at a low dose regularly increase at day 7, 14 and 28 depending on the expected benefits from a higher dose and potential dose-dependent side effects. (Table 3).

**Table 3 Tab3:** Doses escalation during the study follow up

		**Starting doses – Day 0**	**Day 7**	**Day 14**	**Day 28**
		Mirtazapine: 15 mg Escitalopram: 10 mg (or 5 mg for patients older than 65)			
Excessive drowsiness (CTCAE grade 1 or rated moderate or severe using the ASEC)			*For patients under 65 in the escitalopram arm: decrease to 5 mg*		
			*For every other patients: Stop the treatment*		
Any severe adverse effect or serious adverse event (CTCAE grade > 3 or rated severe using the l’ASEC)			*Stop the treatment*		
Moderate adverse event (CTCAE grade 2 or rated moderate using the ASEC)			Decrease the dosage (Or treatment stop if already at the lower dosage)		
Mild adverse event (CTCAE grade 1 or rated mild using the ASEC)			No dose adjustment		
No adverse event	Inadequate symptoms’ control (ESAS > 3)		No dose adjustment (or increase the dosage if escitalopram has been started at 5 mg)	Increase the dosage	
	Adequate symptoms’ control (ESAS ≤ 3)		No dose adjustment		

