#### Follow-up procedure

Follow-up will be made on a regular basis during a 56-day period.

Patients will be called by a research assistant on days 7 and 14 to screen for side effects using the ASEC scale. If any adverse event is screened a clinical opinion will be sought for dose adaptation based on predefined criteria. On day 14, escalation of dose will be prescribed by the PI if symptoms are still under controlled (the corresponding ESAS12-F subscale rated over 3) and in the absence of limiting side effect evaluated using the ASEC and Common Terminology Criteria for Adverse Events V4.0.

Clinical assessment will occur on day 28 (more or less 3 days). This assessment is meant to be made physically; however, if the patients’ condition of public-health situation demands it, it will be performed using teleconsultation. During this consultation, the patient will fulfil the EORTC QLQ-C30, ESAS -12F, HADS-D, and ASEC questionnaires. The PI will weigh the participant, count the number of pills that remains to the patient, evaluate the Performance Status and fill the MARDS. Considering all available data (tolerance, side-effects and symptom control), the PI will make the decision regarding the escalation of treatment dose.

During the final evaluation, on day 56, the patient will fulfil the EORTC QLQ-C30, ESAS -12F, HADS-D, ASEC, and factor 1 of the Medication Adherence Rating Scale (MARS) questionnaires. The PI will weigh the participant, count the number of pills that remains to the patient, evaluate the Performance Status and fill the MADRS.

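### Two CTCAE thresholds in Table 3 do not fit the table's own scale: no row names grade 3, and the drowsiness row pairs grade 1 with moderate or severe ASEC ratings

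*Protocol article*

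**What the plan says.** Table 3 (Methods, Intervention and comparator) lists dose actions by type and severity of adverse event. Four rows matter here.

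- **Drowsiness:** "Excessive drowsiness (CTCAE grade 1 or rated moderate or severe using the ASEC". Escitalopram patients under 65 go down to 5 mg. The rest, which includes all mirtazapine patients, fall under "For every other patients: Stop the treatment".
- **Severe effect or serious event:** "CTCAE grade > 3 or rated severe using the" ASEC. The action is to stop.
- **Moderate:** "Moderate adverse event (CTCAE grade 2 or rated moderate using the ASEC". The action is "Decrease the dosage (Or treatment stop if already at the lower dosage".
- **Mild:** "Mild adverse event (CTCAE grade 1 or rated mild using the ASEC". The dose is not changed.

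The Follow-up procedure section relies on such rules for the day 7 and day 14 calls: "If any adverse event is screened a clinical opinion will be sought for dose adaptation based on predefined criteria". It allows escalation on day 14 only "in the absence of limiting side effect evaluated using the ASEC and Common Terminology Criteria for Adverse Events V4.0". Table 3 is the only place where the article prints these rules, and no other section restates or corrects the grades.

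**The concern.** A severity ladder should cover every grade, and its two scales should agree on what each step means. Table 3 fails on both counts. A grade 2 event has an action attached to its grade, but the worse grade 3 event does not. For drowsiness, the CTCAE trigger is at the grade that the table elsewhere treats as mild, while the ASEC trigger in the same row starts at moderate.

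These are printed stopping thresholds, not detail left to a fuller document. What is at stake is dosing safety and uniform dosing across centres. A site that follows the printed number does not stop at grade 3 because of the grade, and it may withdraw mirtazapine for drowsiness that the patient rates as mild.

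**Working it through.** No computed figure in the article is in dispute, and the sample size plays no part. The check reads Table 3 in both directions.

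**1. Row to threshold, as printed**

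| Row | CTCAE grade | ASEC rating | Action |
|---|---|---|---|
| Drowsiness | 1 | moderate, severe | escitalopram under 65: to 5 mg; all others: stop |
| Severe or serious | above 3, so 4 and 5 | severe | stop |
| Moderate | 2 | moderate | decrease, or stop at lowest dose |
| Mild | 1 | mild | none |

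**2. Threshold to row**

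| Level | Rows that name it |
|---|---|
| CTCAE 1 | drowsiness, mild |
| CTCAE 2 | moderate |
| CTCAE 3 | none |
| CTCAE 4, 5 | severe or serious |
| ASEC mild | mild |
| ASEC moderate | drowsiness, moderate |
| ASEC severe | drowsiness, severe or serious |

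Grade 3 is the only gap on either scale. The mild and moderate rows fix the table's pairing as grade 1 with mild and grade 2 with moderate. The drowsiness row is the only one to pair grade 1 with anything higher.

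**3. When the printed numbers change the action**

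- *Grade 3, not drowsiness.* If the ASEC rating is severe, the stop row applies and the gap has no effect. If it is moderate or mild, the only bracketed thresholds met are those for a decrease or for no change. With no ASEC rating, no bracketed threshold is met. In these last cases a stop depends on the row label or on clinical judgement.
- *Drowsiness.* If the ASEC rating is moderate or severe, the drowsiness row applies whatever the CTCAE grade. If it is mild or absent, grade 1 triggers the drowsiness row, grade 2 meets only the moderate row, and grade 3 has no row of its own.

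The thresholds therefore matter when the ASEC rating is absent or below the level that fits the grade or that the row pairs with it. For grade 3 that means below severe. For the drowsiness row it means below moderate, which includes grade 1 with ASEC mild, a combination that the general rows treat as agreement.

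**4. Example: drowsiness with no ASEC rating, bracketed thresholds only**

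Assumptions: 15 mg mirtazapine and 5 mg escitalopram are the lowest doses, and the drowsiness row overrides the general rows when it is met.

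| Starting dose | Grade 1 | Grade 2 | Grade 3 | Grade 4 |
|---|---|---|---|---|
| Mirtazapine 15 mg | stop | stop | no row | stop |
| Escitalopram 10 mg, under 65 | to 5 mg | decrease | no row | stop |
| Escitalopram 5 mg, over 65 | stop | stop | no row | stop |

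This shows the break in the ladder. It leaves the words of the stop row's label out of account and is not a frequency.

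**5. Could the ASEC rating be absent or lower?**

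Table 1 schedules the ASEC on days 0, 7, 14, 28 and 56. An event between contacts, including the 56 − 28 = 28 days after day 28, has no scheduled rating at onset. On days 7 and 14 a research assistant takes the ASEC by telephone. Outcomes assessment has adverse events graded by CTCAE as well, so two separate ratings exist and can differ.

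**6. Extraction**

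Both a greater-than and a less-than-or-equal sign survive in the ESAS rows of Table 3, so a symbol lost from the text is an unlikely explanation.

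**The case against.** The strongest reply is that the stop row is defined by its label, which covers severe effects and serious events. Grades 1 and 2 are taken by mild and moderate, so anything worse belongs in the severe row, and no row tells a clinician to continue after a severe event. The bracket also offers the ASEC as an alternative, and Follow-up procedure requires a clinical opinion for any event found at screening. This stands. A reader might infer that grade 3 events have no stopping rule, or that patients would stay on full dose. The documents do not support that: only the CTCAE grade fails to trigger the stop.

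A second reply is that Table 3 acts on days 7, 14 and 28, when the ASEC is scheduled, so an earlier event can be rated at the next contact. This narrows the case of an absent rating but does not remove discordant ratings. The documents do not show how often the scales differ.

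A third reply is that a stricter drowsiness rule may be deliberate, since stopping early is cautious, and that grade 1 may be meant as a minimum. That is possible. But a deliberate rule would be expected to lower the ASEC trigger to mild as well, and the row's heading speaks of excess. The mismatch is certain; which value is wrong is not.

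A reader might also infer uneven discontinuation between arms, because mirtazapine patients stop where escitalopram patients under 65 only reduce. The wording allows this, but the article gives no rates, so neither its occurrence nor its size can be claimed.

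Finally, the article condenses a full protocol that sites would use and that may print other values. That limits the operational consequence but does not make the printed thresholds right.

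**Conclusion.** The point holds as an internal inconsistency in Table 3. No row names CTCAE grade 3, and the drowsiness row's CTCAE trigger sits below its own ASEC levels. Both can be read from the table without outside sources.

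The size is modest. For grade 3, the row label, a severe ASEC rating and clinical judgement remain as routes to a stop. The printed numbers decide the action only when the ASEC rating is absent or below the level that fits the grade or that the row pairs with it, and the frequency of such cases is unknown. The consequence is for dosing safety and consistency; none is claimed for power, endpoints or the primary analysis.

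Two things are inferred: that the stop row was meant to include grade 3, and that the drowsiness row was meant to start at grade 2. The first follows closely from the table's pairing. The second is only the more likely of two readings. The text at hand also does not show which day columns the drowsiness action spans, so nothing here rests on its use after day 7.

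**What to change.** 1. In the stop row, print CTCAE grade ≥ 3.
2. In the drowsiness row, make the two triggers agree. Either use CTCAE grade ≥ 2 with the printed ASEC levels or, if a stricter rule is intended, use grade ≥ 1 and add ASEC mild. The clinical team should confirm which.
3. State that the drowsiness row governs drowsiness. As printed, drowsiness rated severe on the ASEC in an escitalopram patient under 65 meets both the reduction to 5 mg and the stop row. The clinical team should decide whether the reduction stands or treatment stops.

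With items 1 and 2, every grade from 1 to 5 has a row. With the first option in item 2, the drowsiness row also matches the pairing used in the rest of the table.

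The cost is a correction to one table, plus a notice to sites if the full protocol carries the same thresholds. Sample size, endpoints and analysis do not change.
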